### Data analyses

Most analyses will be conducted using the software program Statistical Package for the Social Sciences (SPSS). The descriptive analyses will be carried out using standard methods. If necessary, outliers will be checked and winsorized before analyzing. Differences in baseline characteristics between both experimental groups and the care-as-usual-only group will be analyzed and results will be controlled for these differences if needed. For analyzing the primary (social participation on three domains), mediation (psychosocial functioning and self-determination), and predictor (demographic factors and personality) outcomes, ANOVA repeated measures or multilevel analyses will be used. The primary outcomes of participants in both experimental groups will be compared separately from the care-as-usual-only group. Pre-test, post-test, and follow-up will show the change in quantity and quality of social participation, psychosocial functioning, and self-determination as compared with the care-as-usual-only group, over time. Feasibility of the Mentor Support intervention will be analyzed using descriptive analyses. General mixture modeling with M-plus [58] will be used to examine the impact of the Mentor Support intervention on subgroups. Analyses and reporting of the results will be done according to the CONSORT Statement guidelines.

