### Randomization

Upon signing the informed consent, before randomization, participants agree to be allocated to one of the three groups. An independent researcher will randomly assign participants at an individual level to one of the three arms of this randomized controlled study. The allocation will take place with a computerized random number generator after the baseline measurement and before the start of the intervention. Randomization stratification on the important factor of geographic proximity will be used to make sure there is equal allocation to regions. Blocking randomization in each region with a block size of 15 participants will be used to strive for regional groups with the same size. The independent researcher will keep the results of the randomization until the study is completed and all eligible participants are allocated. During the study the primary researcher and participants are not blinded. Only the researchers measuring the post-test and follow-up will be unaware of who is allocated to which arm.

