#### Control variables

Degree of visual impairment, mobility, and treatment integrity will be measured and used as control variables.

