### Sample size

The total sample size is based on the expected differences in outcome measures between participants assigned to the experimental arm receiving Mentor Support and the care-as-usual-only arm. For testing the significance of the between-subject factor (primary hypothesis) a sample of 120 participants (40 in each condition) is necessary to achieve an adequate power of .85 within a medium effect size (d = .5) between the conditions over time with a significance level of .05. Due to dropout or unexpected organizational aspects the number of participants could drop to as low as 108 to achieve a high power of .80. To answer the research question concerning the influence of potential mediators or predictors on the effectiveness of Mentor Support, several repeated measures within-between interaction analyses will be performed. Based on a significant level of .05 and a power of .85 (*f* = .25), a total sample size of 110 is needed.

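### Adjustment depends on chance baseline differences, and neither the T1 outcome score nor region is a fixed covariate; the cost is lost precision and open discretion, not inflated type I error

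*Protocol article*

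**What the plan says.** Data analyses states the covariate rule: differences in baseline characteristics between the experimental arms and care-as-usual "will be analyzed and results will be controlled for these differences if needed". It gives no threshold, no list of variables and no person who decides.

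The same section leaves the primary model open ("ANOVA repeated measures or multilevel analyses will be used") and treats T1 as the first of three outcome occasions: "Pre-test, post-test, and follow-up will show the change in quantity and quality of social participation". It compares each mentor arm separately with care-as-usual, whereas the main hypothesis (Hypotheses) sets Mentor Support as a whole against care-as-usual.

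Control variables does fix a list: "Degree of visual impairment, mobility, and treatment integrity will be measured and used as control variables". It does not say which models these enter. Treatment integrity is taken from forms that mentor-mentee dyads complete after each meeting (Treatment integrity).

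Randomization says "Randomization stratification on the important factor of geographic proximity will be used", and adds "Blocking randomization in each region with a block size of 15 participants". No section puts region into an analysis model.

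**The concern.** Selecting covariates because the arms happen to differ on them picks variables for imbalance. What makes a covariate useful is its relation to the outcome. The T1 score of the same measure is usually the strongest such variable, yet under this rule it would become a covariate only when chance had separated the arms on it. The adjusted model would then differ from one realisation of the randomisation to the next, and the wording leaves room to decide after the differences have been seen.

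Two further matters follow. The trial measures T1 before allocation and stratifies by region, but secures the benefit of neither in the model. And one of the three variables that are fixed, treatment integrity, has no value for a participant who has no mentor.

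At stake is the power of a trial that calls its own sample relatively small (Discussion), and the credibility of an adjusted result whose covariates were not set in advance.

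**Working it through.** **1. The plan's own figure.** Sample size gives power .85 at N = 120 and .80 at N = 108 for d = .5 and alpha .05. Take the between-subject factor of a repeated-measures ANOVA with 3 groups, 3 occasions and f = d/2 = .25, and assume a correlation of .5 between occasions (not in the article). The noncentrality is f² × N × 3 / (1 + 2 × .5).
- N = 120: .0625 × 120 × 3 / 2 = 11.25; power .851.
- N = 108: .0625 × 108 × 3 / 2 = 10.125; power .809.

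Both figures reproduce. This test averages over all occasions, T1 included. It is neither the change analysis nor a T1-adjusted one, so .85 is not the benchmark for step 3.

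**2. Variance with and without T1 as covariate.** Set the outcome SD to 1 at each occasion, with T1-T2 correlation ρ.
- Change from T1 to T2 (the time-by-arm contrast): V = 2(1 − ρ).
- T2 adjusted for T1: V = 1 − ρ².
- Ratio adjusted/change: (1 + ρ)/2 = .65, .75, .85 at ρ = .3, .5, .7.

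**3. Power.** SE = √[V(1/n₁ + 1/n₂)]; noncentral t with noncentrality .5/SE, n₁ + n₂ − 2 degrees of freedom, two-sided .05. Example at ρ = .5, 40 v 40: change has V = 1.00, SE = √(1.00 × .05) = .224, noncentrality 2.236, power .598. Adjusted has V = .75, SE = √(.75 × .05) = .194, noncentrality 2.582, power .722.

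| ρ (assumed) | 40 v 40, change | 40 v 40, T1-adjusted | 80 v 40, change | 80 v 40, T1-adjusted |
|---|---|---|---|---|
| .3 | .463 | .639 | .581 | .766 |
| .5 | .598 | .722 | .726 | .841 |
| .7 | .814 | .871 | .911 | .948 |

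The 40 v 40 columns match the separate comparisons in Data analyses; the 80 v 40 columns match the main hypothesis.

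**4. The conditional rule applied mechanically.** Suppose T1 is adjusted for only when its baseline test gives p < .05 (an assumed criterion). With correct randomisation that happens in about 5% of trials. Simulation, 40 v 40, 40,000 replicates:
- Power at ρ = .5 is about .61, whether the default is change or T2 alone, against .72 when T1 is always adjusted.
- Type I error is between .036 and .048 over the correlations and defaults tried, so at or below nominal.

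**5. Region.** The share of outcome variance that region explains is not given; assume 1% to 10%. By normal approximation for 40 v 40, power is .609 to .615 without region and .613 to .654 with it, a gain of .004 to .040. The true level of the unadjusted test is .049 to .039, that is, slightly conservative.

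**6. Treatment integrity.** Allocation precedes matching and the first meeting, and the forms are completed by dyads. The variable is therefore post-randomisation and exists only in the two mentor arms. It can describe delivery or serve analyses within those arms, but cannot be a covariate in a comparison with care-as-usual.

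**The case against.** The strongest reply is that the plan already fixes three covariates and already uses T1. Both are true. The covariate set is thus only partly driven by imbalance, and T1 as a first occasion is a valid analysis. The multilevel option could also constrain baseline means to be equal across arms, which would recover most of the gain in step 3. But no such model is specified, and the loss applies to the analysis of change that the article describes. It shrinks as the correlation rises.

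The second reply is that a stratification factor is normally left to the analysis plan. Taken alone, the absence of region is silence and not a fault, and its effect is small. It belongs in the fix because the covariate sentence has to be rewritten anyway.

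Some stronger readings are tempting and not supported:
- *The rule inflates type I error.* Applied mechanically, it does not (step 4). Reporting whichever of the change and T1-adjusted results had the smaller p would give roughly .067 to .078 in simulation, but the article proposes no such choice.
- *The unblinded primary researcher picks the covariates.* Randomization says that researcher is not blinded; no section says who selects covariates.
- *A spurious difference is more likely than not.* With independent tests at .05, the chance of at least one is 40% for 10 characteristics and 64% for 20. The article states neither a number of tests nor a threshold, nor that significance tests will be used.

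**Conclusion.** The point stands as a fault in a rule the article states, and does not depend on what an unseen analysis plan may add. Adjustment is tied to observed baseline differences without a criterion, the T1 score is not secured as a covariate, and one fixed control variable cannot serve in the between-arm comparison.

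The size depends on an unreported correlation. Over .3 to .7, with d = .5 and one post-test, the power forgone is about 18, 12 and 6 points for each 40 v 40 comparison (.639 − .463, .722 − .598, .871 − .814), and about 19, 12 and 4 points for the pooled 80 v 40 contrast. Region adds at most about 4 points under the range assumed. The calculations assume equal variances at both occasions and no dropout.

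**What to change.** Replace the conditional sentence in Data analyses with:

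> All primary models adjust for the T1 value of the outcome (or constrain baseline means to be equal across arms), for region, and for degree of visual impairment and mobility at T1. Baseline characteristics are described by arm and do not determine the covariates.

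Amend Control variables so that treatment integrity is not a covariate in any between-arm model and is kept for describing delivery within the mentor arms.

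The cost is wording only. T1 is measured on everyone before allocation, region is known at randomisation, and the other two variables are already collected. Trial status reports recruitment and data collection still in progress, so the covariates can be fixed before outcomes are analysed.

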### Data management and monitoring

Data will be collected using online survey software called Qualtrics. This software makes it easy to transport data to other software programs such as SPSS to analyze data. There is no risk of participants being involved in data management and, therefore, no Data Monitoring Committee has to be established. This study is financially supported by Vereniging Bartimeus Sonneheerdt and ZonMw, the Dutch Organization for Health Research and Development program InZicht and embedded in the EMGO+ Institute for Health and Care Research of the VU University Medical Center. These three organizations will conduct site visits or audits to check the progress of the study throughout the project. The EMGO+ Institute provides an electronic quality assurance handbook to uniform the conduct and safeguard the quality of research within the institute, and this handbook will be consulted during this study.

### Protection of data privacy

All participants in the study will be assigned a participant number. Key lists will be stored separately from the data and will be deleted after final data analyses. Data will be analyzed in a way such that no conclusions can be drawn about individual participants. All data are stored on lockable laptops in lockable cabinets in lockable rooms. All researchers, research assistants, and students working within the project sign a statement in which they declare not to disclose any information about research participants to a third party.

### Publication policy

The results of this study will be published in international journals. To make the results also available for Dutch service providers, professionals, and participants, we plan to publish the results in Dutch journals. Results will also be presented at international scientific conferences, as well as at national conferences within the field of youth care and visual impairments.

### Ethical considerations

The study protocol has been approved by the Ethics Committee of the VU University (VCW.1310.010). Changes within the study procedures will first be proposed to the Ethics Committee.

## Discussion

This study aims to improve social participation of adolescents with VI and compares two experimental groups with one care-as-usual-only group. A secondary objective is to distinguish if psychosocial factors and self-determination mediate this process and if the two experimental groups lead to different social participation outcomes. A strength of this study is the added value of the use of two types of mentors to improve social participation. This might give us more insight into the importance of experiential expertise during mentoring, especially during the transition phase from adolescence to young adulthood. This effect is still uncertain and has never been studied before. Also, the lack of studies about the effectiveness of mentoring interventions to improve social participation makes this study unique. Targeting three domains of social participation is another strength of this study. It provides information about the outcome factors of mentoring and the connectedness of these domains within social participation. A fourth strength of this study is the use of several well-known, frequently used, reliable questionnaires which measure a large number of key variables and factors. This provides the opportunity to look at predictors and mediating effects over time and to compare results from this study with other (international) studies. Another strength of this study is that the target group is a less frequently studied group of persons. Most of the studies concerning people with VI examine developmental problems such as language development, locomotion, and academic achievement. But the total construct of social participation is mostly neglected, especially during the transition phase from adolescence to young adulthood. This study may therefore expand knowledge about social participation development. Finally, a strong aspect of this study is the use of the Internet during the intervention, with a specially designed website. This allows information to be spread easily and all participants to be contacted in the same way. This is especially salient because participants in this study live in several (sub) urban locations throughout the Netherlands, and also because adolescents are likely to be extremely comfortable with web-based interactions and information flow.

One limitation inherent in this study may be the risk of selective attrition during the relatively long period of 18 months for which the participants are connected with the study. During the Mentor Support intervention mentees could drop out of the study for several reasons, such as moving to another part of the Netherlands, parental concerns, or health reasons. Dropout from the care-as-usual-only group may occur directly after the primary researcher has informed them about the results of the randomization and after 12 months with T2. All participants receive and sign an informed consent whereby they are informed in advance about the possibility of ending up in the care-as-usual-only group. This is also mentioned in the first letter or brochure that they receive. This may prevent dropout from the care-as-usual-only group. Another limitation of this study could be the relatively small sample size, due to the small population size. This could lead to problems with making firm conclusions about predictors and mediating study findings. Finally, a limitation could be to find enough mentors in the same region of the country where the participant lives. In this case more mentors are probably needed than the number 40 that we have described above.

In conclusion, this study will gain knowledge about the effectiveness of a mentoring intervention (Mentor Support) for adolescents with visual impairments to improve their social participation. Three conditions are included to test the importance of disability-specific experience. In addition, this study will also give more insight into the pathways to successful social participation, several predictors, and the mediating effects of psychosocial functioning and self-determination.

## Trial status

The study started in December 2012. After being granted permission by the Ethics Committee of the VU University to start including participants, the first research participants were included in September 2014. At this time, data is being collected from the first wave of 58 participants. Currently, recruitment and data collection are still in progress. We expect the main RCT results to be published at the beginning of 2018.

## Abbreviations

BPNSF: Basic Psychological Need Satisfaction and Need Frustration Scale
CERQ: Cognitive Emotion Regulation Questionnaire
DPAL: Degree of Peer Activity List
ICF: International Classification of Functioning, Disability and Health
MSFU: Multidimensional Scale of Facebook Use
NAS: Nottingham Adjustment Scale
PNL: Personal Network List
RCT: Randomized Controlled Trial
RSES: Rosenberg Self-Esteem Scale
SPSS: Statistical Package for the Social Sciences
T1: First assessment
T2: Second assessment
T3: Third assessment
USA: United States of America
VAP: Visual Activities and Participation
VI: Visual Impairments
